# **STUDY OBJECTIVES**

**Objective 1:** Develop a dissemination and implementation strategy to introduce SVA-SAT+TA that effectively accounts for the heterogeneity of the client, provider, and system inputs.

**Objective 2:** Deliver the SVA-SAT+TA intervention at scale in ten reproductive health clinics and evaluate implementation using the RE-AIM framework.

**Objective 3:** Compare the cost and budget impact of SVA-SAT+TA to SVA-SAT using cryotherapy.

#

# **STUDY DESIGN**

We shall use a stepped wedge design to evaluate the introduction of thermal ablation technique for treatment of women who screen positive for precancerous lesions of the cervix to ten reproductive health facilities in Kenya, using Implementation Science framework (CFIR & RE-AIM) to examine implementation process and adoption. In addition, we will use Organizational Readiness for Implementing Change (ORIC) survey tool to assess readiness and include an end user satisfaction survey at each facility at the end of each wave.

**Study Population:**

- AIM 1:
  - 55 IDI among health care providers, policy makers and end users
- AIM 2:
  - 30 HCP in small group discussions among healthcare providers per facility conducted across implementation wave (3 - HCP per facility)
  - Approximately 30 IDI among health care managers
  - 20 IDI among screen positive women treated (2- per facility)
  - 90 providers and managers to assess ORIC
  - 360 screen-positive women enrolled to the HPV sub-study
  - 3-5 HCP per facility in small group discussions participating in Pre-barrier assessment survey at the end of each intensive implementation wave.

At each reproductive health facility, we anticipate screening 30 women per month for at least 24 months (in the clinics that activate last), for a total of >7,200 women. Estimating a 5% screen positive rate, each facility will have nine screen-positive women per wave, with an estimate 360 screen positive for data abstraction. A sub-set of 360 women will be enrolled for the HPV-sub study.

Estimated total number of study participants enrolled: Approximately 595

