**Objective 2:**

**Deliver the SVA-SAT+TA intervention at scale in RH clinics and evaluate implementation using the RE-AIM framework**.

*Approach*: We will introduce the SVA-SAT+TA into RH clinics using a stepped-wedge study design and rigorously evaluate how effectively this intervention is disseminated and implemented. Key endpoints will include:

a) (REACH) Proportion of the clinics reached, providers trained;

b) (EFFECTIVENESS) Intervention effect on SVA-SAT process measures: number of screen positive women identified per month, treatment completion rate compared to pre-intervention, and the patient-level TA fidelity of implementation assessed by testing HPV clearance 6 months post-treatment among 360 randomly selected screen positive women treated with TA;

c) (ADOPTION) Proportion of the clinics incorporating TA into routine care through updated policies and trained provider in practice;

d) (IMPLEMENTATION) Determine core components of the SVA-SAT+TA intervention and describe drivers of success/failure using the Consolidated Framework for Implementation Research;

e) (MAINTENANCE) Proportion of clinics that continue to provide and sustain SVA-SAT+TA services 6-12 months after intervention implementation.

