**Power and sample size** According to data on cervical cancer screening and preventive treatment for Kiambu County from 2017-2019, 20% of cervical cancer screening clients who screened positive received cryotherapy or LEEP. Routine data from our proposed study facilities show an average of 30 clients per month were screened at each facility in the first three months of 2020 (**Table 3**), corresponding to approximately 10% of eligible clients. The primary effectiveness outcome is the proportion of screen-positive women who receive same day ablation treatment. Assuming six-month waves, 30 clients screened per month and a 5% screen positive rate, we will have an average of 9 screen-positive women per facility per wave. Assuming an intracluster correlation coefficient of 0.2, alpha=0.05 and 20% treatment coverage pre-intervention, we will have 80% power to detect a three-fold increase to 60% treatment coverage using thermal ablation (R (v 3.6.3) package swCRTDesign (v 3.1)). We estimate that 90% of screen positive women will be eligible for ablative treatment.(49)

**Data analysis**: The primary analysis of proportion of screen positive women who are treated pre vs post- intervention. We will use weighted least square methods appropriate for this facility-randomized three-wave step wedge design, where all clinics begin in the control condition, We will consider the intervention effect to be fixed throughout the exposed period, but random effects per facility and wave. To analyze secondary outcomes of increase in proportion of trained providers (the **REACH** outcome) and increase in number screen-positive (secondary outcome) we will use the same analysis approach for the binary and count outcome. Exploratory analysis will examine potential effect modification of facility-level factors such as patient volume, patient to provider ratio, and women screened. Potential multi-level adjustment variables include individual-level factors such as age and access to resources. The HPV sub-study in women treated with TA will assess HPV clearance in HPV-positive women. Assuming 70% of screen-positive women test positive for HPV prior to TA (N = 140), the confidence interval for HPV clearance will be +/-8.1%

- **ADOPTION**

Our primary outcomes for adoption will be

1. the proportion of clinics incorporating TA into routine care through updated policies
2. Proportion of trained providers performing SVA-SAT +TA for screen positive women and

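### The HPV sub-study's 360 TA-treated women equal the protocol's whole screen-positive estimate, are not reached on its own planning figures, and conflict with an interval based on about 200 women

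*Protocol*

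**What the plan says.** The Study Population section sets the volume: "we anticipate screening 30 women per month for at least 24 months (in the clinics that activate last), for a total of >7,200 women". It continues: "Estimating a 5% screen positive rate, each facility will have nine screen-positive women per wave", and then "with an estimate 360 screen positive for data abstraction. A sub-set of 360 women will be enrolled for the HPV-sub study".

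Objective 2 in the Executive Summary describes the sub-study endpoint as "HPV clearance 6 months post-treatment among 360 randomly selected screen positive women treated with TA". The Effectiveness text under Table 4 also gives about 360 women treated with TA. Table 4 and Human Subjects Considerations repeat that the women are chosen at random. The eligibility statement in the HPV Sub-Study section, by contrast, asks for treatment of a pre-cancerous lesion without naming TA.

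The Power and sample size paragraph repeats the yield ("we will have an average of 9 screen-positive women per facility per wave"). It takes 60% as the treatment coverage with TA, against 20% before, and puts eligibility for ablation at 90%. The data analysis paragraph that follows assumes 70% of screen-positive women are HPV-positive, gives N = 140, and states an interval of ±8.1 points for clearance. The clearance target is 60%.

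The Aim 2 overview activates 3–4 of the ten clinics at each of three steps about six months apart. Every clinic first contributes at least six months of control data.

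**The concern.** A sample and its source population have the same size. The 360 women expected for data abstraction are all the screen-positive women in the estimate. The sub-study needs 360 from a narrower group: those seen after their clinic has TA, treated with it, consenting, and returning at six months. If the pool is smaller than the target, staff would take every willing woman, and a consecutive series would be reported as a random sample.

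The figure also drives planning. It makes up most of the roughly 595 participants in the stated enrolment total, and it sets the scale of HPV testing, follow-up and consent work. The interval quoted for clearance rests on a different number of women, so a reader cannot tell which size the sub-study is meant to have.

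**Working it through.** **1. Reproduce the stated total.** 30 per month × 24 months × 10 clinics = 7,200 screened; 7,200 × 0.05 = 360 screen-positive. Equivalently, 9 per clinic per six-month period × 4 periods × 10 clinics = 360. The protocol's figure reproduces exactly.

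**2. Count the clinic-months with TA.** With six months of baseline and steps six months apart, step 1, 2 and 3 clinics have 18, 12 and 6 months of TA by the end of wave 3.
- Allocation 4/3/3: 4×18 + 3×12 + 3×6 = 126 clinic-months
- Allocation 3/4/3: 3×18 + 4×12 + 3×6 = 120
- Allocation 3/3/4: 3×18 + 3×12 + 4×6 = 114

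So 114–126 of the 240 clinic-months are exposed. Each further 12 months of maintenance adds 10 × 12 = 120.

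**3. Convert to TA-treated women.** The planning yield is 30 × 0.05 = 1.5 screen-positive women per clinic-month, with 60% treated.

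| Enrolment ends | Exposed clinic-months | Screen-positive (×1.5) | Treated (×0.6) |
| --- | --- | --- | --- |
| End of wave 3 | 114–126 | 171–189 | 103–113 |
| + 12 months' maintenance | 234–246 | 351–369 | 211–221 |
| + 24 months' maintenance | 354–366 | 531–549 | 319–329 |

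None reaches 360, and refusals and six-month losses are not yet deducted. At the 90% eligibility ceiling, the end-of-wave-3 figure is 154–170.

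**4. Try kinder assumptions.**
- *Eligibility not limited to TA.* Add control-period women treated at 20%: 102.6 + 0.2×189 = 140.4 to 113.4 + 0.2×171 = 147.6, or about 140–148 by the end of wave 3.
- *Positivity observed in Table 3.* 70 positives in 10 clinics × 4 months gives 1.75 per clinic-month. By the end of wave 3, 120–132 are treated. With 24 months of maintenance, 354–366 × 1.75 × 0.6 = 372–384.
- *24 months counted from activation in the last clinics.* Steps 1, 2 and 3 then have 36, 30 and 24 months of TA, or 294–306 clinic-months and 441–459 screen-positive women. Treated: 265–275 at 60%, 397–413 at 90%.
- *Screening doubled to the 20% Reach target (3.0 per clinic-month).* 205–227 treated by the end of wave 3; 421–443 with 12 months of maintenance.

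Some of these pass 360. The second needs 360/384 to 360/372, about 94–97%, of treated women enrolled. The third, at 90% treated, needs 360/413 to 360/397, about 87–91%.

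**5. Check the interval.** Half-width = 1.96 × √(0.6 × 0.4 / n).
- n = 140: 8.1 points, as stated. But 140 / 0.70 = 200 women, not 360.
- n = 0.70 × 360 = 252: 6.0 points.
- About 105 treated (end of wave 3): n ≈ 74, about 11 points.
- About 215 treated (12 months' maintenance): n ≈ 150, about 7.8 points.

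**The case against.** The strongest reply is that the stated volumes are minimums: at least 24 months, and more than 7,200 women. The remark about the clinics that activate last makes good sense if the 24 months run from activation. In that case the first 360 would be a lower bound on women screened positive under TA, not a total that includes control periods. Abstraction continues into maintenance, outreach is planned to raise demand, 60% is a target and a detectable effect and not a forecast of yield, and 360 is called an estimate. The sub-study is descriptive and tests no hypothesis.

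Much of this stands, and it rules out three stronger conclusions that a reader might draw.

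- *That 360 TA-treated women can never exist.* The text does not support this. The volumes are minimums, and step 4 shows routes to 360.
- *That 360 is reached only if screening doubles.* This is not so. Table 3's positivity with 24 months of maintenance gives 372–384 treated, and 24 months after activation with 90% treated gives 397–413.
- *That clearance will be estimated much less precisely than stated.* This holds only if enrolment stops at the end of wave 3, which no passage says. With 12 months of maintenance, 211–221 treated women give about 148–155 HPV-positive and 7.7–7.9 points, slightly narrower than the stated 8.1.

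What the reply does not remove is the shared number. Even if all 360 screen-positive women were seen under TA, 216 would be treated at 60% and 324 at 90%. Nor does it explain an interval built on 200 women.

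**Conclusion.** The point holds on the plan's own stated figures. The expected screen-positive count and the sub-set drawn from it are both 360, so a random selection of 360 TA-treated women does not follow from the estimate. At 1.5 screen-positive women per clinic-month, a three-step rollout and 60% treated, the yield falls short even after 24 months of maintenance, with full consent and no losses. Reaching 360 takes more favourable positivity, treatment or screening, and in the first two routes nearly full enrolment.

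The protocol also carries two incompatible sub-study sizes: 360 women, and the 200 implied by N = 140.

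The size of the shortfall depends on when enrolment ends. The readable text does not say, and Figure 3 and the study timeline could not be seen. The counts assume six months of baseline and evenly spaced steps. The primary outcome, treatment completion, is unaffected, so this should be fixed but is not critical.

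**What to change.** Define the sub-study as all consenting TA-treated women and drop the random selection. State the enrolment window. Replace 360 with the number the rollout is expected to yield over that window, and give the matching interval. As examples on the planning figures, before refusals and losses: about 105 women by the end of wave 3, with about ±11 points; or about 215 with 12 months of maintenance, with about ±7.8 points, consistent with the stated ±8.1. The sponsor should choose the window; these numbers are not replacements to copy in.

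Reconcile the following places: Objective 2; Study Population, including the total of about 595; Table 4 and the Effectiveness text; Power and sample size with Data analysis (N = 140); the HPV Sub-Study eligibility, which does not name TA; the list of data to be collected in the Data section; and Human Subjects Considerations.

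The cost is a change of wording and a smaller stated sub-study. No extra enrolment is needed, and if enrolment runs through 12 months of maintenance with few refusals or losses, the stated precision is kept.

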# **IMPLEMENTATION PLAN**:

***Aim 1:* Develop a dissemination and implementation strategy to introduce SVA-SAT+TA that effectively accounts for the heterogeneity of the client, provider, and system input*.***

We will use participatory methods to conduct qualitative interviews with clients, front-line health providers, facility managers and policy makers in the Ministry of Health to assess and address barriers and facilitators to SVA uptake and provide information on the introduction of the SVA-SAT+TA intervention through stakeholder engagement, as we have done in previous IS projects.(55) Based on informal engagement with frontline health care workers and managers in the study area, we anticipate openness to the SVA-SAT+TA intervention. This baseline engagement and guidance from the frontline health workers, clients, and other stakeholders will allow structural barriers or any other unforeseen challenges to implementation to be identified early on in the project.

In-depth qualitative interviews We will use the CFIR interview guide tool *(*[*https://cfirguide.org/wp-content/uploads/2019/08/cfirconstructs.pdf*](https://cfirguide.org/wp-content/uploads/2019/08/cfirconstructs.pdf)*)* to develop questions to explore barriers and facilitators to potential *adoption, delivery, and sustainment* of the SVA-SAT+TA intervention. Four domains (and constructs) of the original CFIR will inform both data collection and analysis: intervention characteristics (relative advantage, adaptability, complexity, cost), inner setting (tension for change, compatibility, relative advantage, readiness for implementation), characteristics of individuals (self-efficacy, knowledge and beliefs) and implementation process (planning, engaging, executing). We will also include the additional domain of “Characteristics of Systems’ to capture the intrinsic influence of the following constructs: systems architecture, external funding agent priorities, strategic policy alignment, and resource continuity in global health settings.(59) In addition, the additional constructs proposed for domains of the intervention (perceived scalability) inner setting (team characteristics, collective efficacy) and process of implementation (decision-making), will also be considered. If findings do not fall within these pre-identified constructs of interest, additional constructs will be added inductively using a grounded theory approach. We will interview frontline health providers carrying out CC screening in RH clinics (n= 30). These health providers will be purposively sampled by profession to ensure representation of nurses, clinical officers and doctors who provide reproductive health care as well as a subset with management roles (n= 10). We will also interview two female patients recently screened for cervical cancer in each study facility (n=20) and policymakers (n=5) stationed at the National Cancer Institute and the Division of Reproductive Health at the Ministry of Health of Kenya. Sample size determination in qualitative research rests on maximizing potential for saturation (when new interviews do not meaningfully add to codes and themes already represented in the previously collected data).(60) Our investigative team has extensive experience conducting in-depth interviews, group interviews and focus group discussions with purposefully-sampled health providers.(61-64)

Qualitative data analysis. Interviews will be recorded and transcribed. Transcripts will be uploaded to qualitative data management computer program Dedoose *(*[*https://www.dedoose.com/*](https://www.dedoose.com/)*)* or other qualitative software and analyzed using qualitative content analysis primarily following a deductive approach, using the CFIR as a guiding framework (as described above). Two coders will independently code facility level transcripts for each CFIR construct. Coding will be compared across the two coders and differences discussed to agree on final coding. With input from a qualitative expert, ratings that will be assigned for each construct within each facility. Ratings will be applied to reflect the positive or negative influence (valence) and the strength of each construct as described previously by Damschroder, et al.(65) Constructs will be coded as not distinguishing between potential for high and low implementation (0), or weakly (+1/-1) or strongly (+2/-2) distinguishing potential for low to high implementation performance.

**STAKEHOLDER WORKSHOP**: We will conduct a one-day stakeholder workshop, in collaboration with the National Cancer Institute to present findings from the qualitative work and introduce our study, specifically the phased introduction of SVA-SAT+TA. Invitees will include representation from the National Cancer Institute, Ministry of Health leadership, county-level reproductive health coordinators, health facility managers and select front line health providers from participating reproductive health facilities that provide VIA. At this workshop, we will invite stakeholders to suggest adaptations to the planned implementation of SVA-SAT+TA that may be necessary in specific local contexts and settings and we will attempt to incorporate ways to include these implementation guidelines for the introduction of SVA-SAT+TA.

Stakeholder meeting size will be approximately 30 – 40 persons who will be divided into three small groups to discuss determinants of implementation. To identify determinants of implementation from the workshop, the research qualitative team will summarize key points from small group deliberations and present these summary findings back to the stakeholders for consensus. We will use this feedback to refine our design to be compatible with facility workflow and systems, aligns with organizational culture and is agreeable to our stakeholders. In addition, we will use a checklist to evaluate the extent to which the deployed implementation strategies during the intensive implementation phase respond to the pre-identified barriers gathered at this stakeholder’s workshop.

***Aim 2:* Deliver the SVA-SAT+TA intervention at scale in RH clinics in Kenya and evaluate implementation using the RE-AIM framework**

Overview. At 10 reproductive health facilities in central Kenya, we will introduce the SVA-SAT + TA intervention developed and refined in Aim 1 in a stepped-wedge fashion and rigorously evaluate how effectively this strategy is disseminated and implemented. In three successive waves, with a new wave starting approximately every six months, we will roll out the intervention at 3-4 clinics per step (Fig 2). A final maintenance phase will permit evaluation of the stability of the intervention over time without direct study inputs.

**Clinic Study Setting:**

We will implement this work in ten health facilities in Embu, Kiambu, Nairobi and Murang’a counties in central Kenya, including urban faith-based , rural and urban health facilities (Table 3). Reproductive health services in the county are led by a county gynecologist and managed by reproductive health coordinator. In large health facilities, a resident gynecologist leads reproductive health services. Services in smaller health facilities are led by a clinical officer or nurse. Reproductive health services in Kenya are mostly offered by nurses. Selected facilities currently use VIA for CC screening, they screened 1237 women over a four month period with a positivity rate of 5% . This sample was purposively selected to be nationally representative and heterogeneous in terms of staffing and service.

**Table 3. Women screened for CC* in selected reproductive health facilities**

| **Facility** | **Women screened**  **(Jan-Apr 2020)** | **Screen positive** |
| --- | --- | --- |
| Kiambu level 4 hospital | 350 | 19 |
| Nyeri level 5 hospital | 206 | 8 |
| Thika level 5 hospital | 117 | 7 |
| Muranga level 5 | 45 | 4 |
| Coptic hospital (urban) | 74 | 8 |
| Karatina level 4 | 181 | 3 |
| Othaya level 4 | 91 | 10 |
| Kiandutu health center | 88 | 5 |
| Ngoliba health center | 10 | 2 |
| Ruiru level 4 | 75 | 4 |
| **Total** | **1237** | **70** |

Average of 300 screened per month and 5% positive

*Cervical cancer (CC)

**Justification for stepped wedge design**. Stepped wedge designs use sequential roll-out of an intervention (to individuals or clusters – in the present case, RH clinics) over time to assess the impact of an intervention, with the order of receiving the intervention determined at random.(56) The design is especially relevant for proven interventions that cannot be withheld ethically, but which cannot necessarily be moved to scale simultaneously in all the clinics with the resources at hand. All clusters are thus offered the intervention by the end of the study, with the order of initiation randomly assigned. Prior to a cluster offering the intervention, the cluster contributes data to the “pre-implementation” (e.g., control) period and once the cluster has begun to implement the intervention, it contributes to the “intervention” period.

This design allows for comparisons of key outcomes in the intervention versus control periods. SVA-SAT+TA is an ideal intervention candidate for a cluster**-**randomized stepped wedge design, given that it is

1) an evidence-based intervention

2) it is logistical and feasible to scale in a phased fashion (which then allows for assessment of implementation with each wave)

3) is implemented at the unit of the facility (i.e., thus we can randomize to phase of implementation at the clinic level).

This design also allows us to quantify the effect of the intervention on screening coverage and treatment effectiveness, while providing data on background changes that might occur during the study period. Finally, this design allows for ample time to assess maintenance of the intervention following withdrawal of intensive study support. Assessing maintenance is critical for interventions introduced to public health facilities, where competing priorities, limited resources, and high patient-to-provider ratios may impede the sustainment of gains made during a study.

***Procedures and Implementation strategies****:* We will implement this work in 4 phases i.e., baseline data period, training phase, intensive implementation phase and maintenance phase.

***Baseline data period****:* We will obtain baseline data on facility-level infrastructure including availability of equipment, supplies, medications as well as current staffing (numbers, cadre and training) and patient flow. Routine data on the proportion of women screened, screened positive, and treated for abnormal lesions will be abstracted monthly, by research staff, for a minimum period of 6 months prior to introduction of the intervention starting with the first wave facilities (Fig**. 3).** During this period, all clinics will contribute data to the “control” arm.

